## Abstract

**Background:**

Besides the classical role of vitamin D on calcium and bone homeostasis, vitamin D deficiency has recently been identified as a contributing factor in the onset of insulin resistance in type 2 diabetes mellitus. However, it is uncertain whether vitamin D deficiency and poor glycaemic control are causally interrelated or that they constitute two independent features of type 2 diabetes mellitus. There are limited clinical trials carried out which measured the effect of vitamin D supplementation on glycaemic control.

The objective of this study is to investigate the effect of vitamin D supplementation on glycaemic control and quality of life in patients with type 2 diabetes mellitus.

**Methods/design:**

In a randomised double-blind placebo-controlled trial conducted in five general practices in the Netherlands three hundred patients with type 2 diabetes mellitus treated with lifestyle advises or metformin or sulphonylurea-derivatives are randomised to receive either placebo or 50,000 IU Vitamin D_3_ at monthly intervals. The primary outcome measure is the change in glycated haemoglobin level between baseline and six months. Secondary outcome measures include blood pressure, anthropometric parameters, lipid profile, insulin resistance, quality of life, advanced glycation end products and safety profiles. Quality of life will be measured by The Short Form (SF-36) Health Survey questionnaire. Advanced glycation end products are measured by an AGE-reader.

**Discussion:**

This trial will be the first study exploring the effect of vitamin D supplementation on both glycaemic control and quality of life in patients with type 2 diabetes mellitus. Our findings will contribute to the knowledge of the relationship between vitamin D status and insulin resistance in patients with type 2 diabetes mellitus.

**Trial registration:**

The Netherlands trial register: NTR3154

## Background

Type 2 diabetes mellitus (T2DM), characterized by peripheral insulin resistance and pancreatic beta-cell dysfunction, represents a worldwide epidemic with significant co-morbidity and mortality due to microvascular and macrovascular complications [1]. Although therapies for T2DM and its co-morbidity have improved over the last few decades, the need for new insights for the prevention and management of T2DM remains needed due to the increased impact of the disease. There is accumulating evidence suggesting that vitamin D status plays a role in many non-skeletal functions including diabetes mellitus [2,3]. The prevalence of vitamin D deficiency is increasing with an estimating number of one billion people worldwide [3]. A recent study in the Netherlands among older people revealed a prevalence of vitamin D deficiency of 47.8% (defined as 25 (OH) D < 50 nmol/l) [4].

Vitamin D is a secosteroid that is obtained from dietary sources, either food or supplements, and exposure to sunlight. It needs to be hydroxylated twice to become biologically active. Vitamin D is transported to the liver where it is first hydroxylated by 25-hydroxylase into 25-hydroxyvitamin D (25 (OH) D). This is the major circulating form used as an indicator of vitamin D status. The second hydroxylation occurs in the kidney by 1α-hydroxylase (1α-OHase), a product of the CYP27B1. Here the largest amount of the biologically active form of vitamin D: 1,25 dihydroxyvitamin D (1,25 (OH) 2D) is formed. Besides its classical role in calcium and bone homeostasis, vitamin D deficiency has recently been identified as contributing factor in the onset of insulin resistance in T2DM [5,6]. In a meta-analysis of observational studies a relatively consistent association between low vitamin D status and the prevalence of T2DM or metabolic syndrome was reported [6]. However, due to confounding and selection bias in epidemiological studies, a causal link cannot be established. To determine whether the relation between vitamin D deficiency and glycaemic control is causal in nature, randomised controlled trials with vitamin D supplementation are needed. To date, only few clinical trials examining this relation, with glycaemic control as primary outcome in T2DM, have been performed [7-13]. The results of these clinical trials are inconsistent mostly due to the small sample size, low dose of vitamin D supplementation and short duration of the trials. Recently, a meta-analysis done by George et al. [14] demonstrated a small effect of vitamin D supplementation on fasting glucose and insulin resistance, with no effect on HbA_1c_. However most of these reviewed studies did not include diabetic patients nor had insulin resistance as primary outcome [15-22]. Therefore, adequately powered, randomised placebo-controlled clinical trials with vitamin D supplementation are needed.

The potential mechanisms by which vitamin D can affect glucose metabolism could be the result of a rapid non-genomic effect or slower genomic effect of serum 25 (OH) D: 1) stimulation of insulin release by the increased expression of vitamin D receptor (VDR) as well as the enzyme 1α-OHase in the pancreatic beta-cells; 2) by binding of the 1,25 (OH) 2D - VDR complex to the vitamin D response element of the insulin receptor at tissue level enhancing insulin responsiveness for glucose transport; 3) suppression of the release of pro-inflammatory cytokines that are believed to mediate insulin resistance [2,5,23]. The latter hypothesis is supported by studies showing an association between low serum 25 (OH) D and increased C-reactive protein levels [24]. Indirectly, vitamin D may influence the extracellular and intracellular calcium regulation which is essential in mediating glucose transport in target tissues.

Another hypothesis may be the influence of serum vitamin D on oxidative stress and thereby reducing the formation of advanced glycaemic end products (AGEs). AGEs are a heterogeneous group of compounds formed nonenzymatically by glycation and oxidation of proteins. In patients with T2DM AGE formation is enhanced as a consequence of a hyperglycaemic and free radical rich environment [25]. The AGE accumulation in the skin, as measured by skin autofluorescence, has found to be an independent strong predictor of microvascular and macrovascular complications in both type 1 and type 2 diabetes [26-28]. Until now, solely a study conducted in diabetic rats is available which demonstrated a relation between AGEs and vitamin D [29].

We proposed to start a RCT with the following objectives:

i. To investigate the effect of vitamin D supplementation on glycaemic control and insulin resistance in patients with T2DM.

ii. To investigate the effect of vitamin D supplementation on health related quality of life measured by SF-36 in patients with T2DM.

iii. To investigate the association between skin autofluorescence and serum vitamin D

## Methods/design

### Study design

We designed a double-blind, randomised placebo-controlled clinical trial among patients with T2DM. We randomly assigned three hundred patients into 1:1 ratio to receive a monthly dose of cholecalciferol 50,000 IU or placebo. The follow-up duration is six months. The study will be conducted in five general practices in and around Alkmaar, a city in north-western Netherlands at latitude 52°.

### Participants

All patients with T2DM at the general practices fulfilling the inclusion criteria at their last visit by the general practitioner will be invited for screening for their eligibility.

### Inclusion/exclusion criteria

Adults (≥18 years) with T2DM, diagnosed according to the World Health Organisation, who are treated with lifestyle advises, metformin, or sulfonylurea-derivatives (SU-derivatives), whether or not in combination, were invited for participation. Serum glycated hemoglobin (HbA_1c_) had to be stable and below or equal to 64 mmol/mol (8.0%) for the last three months without recent changes in hypoglycaemic agents.

The exclusion criteria are: an impaired renal function (estimated creatinine clearance < 30 ml/min measured by the MDRD formula: 186 × (serum creatinine)^ -1.154 × (age)^ -0.203 × 0.742 (if the subject is female) or × 1.212 (if the subject is black)), any granuloma forming disorder, known history of renal stones or hypercalcaemia (serum calcium > 2.65 mmol/l), hypo- or hyperphosphatemia, serum 25 (OH) D < 15 nmol/l or > 150 nmol/l, known intolerance for cholecalciferol, using other antidiabetic treatment as mentioned above, insufficient knowledge of the Dutch language, mental retardation or psychiatric treatment for schizophrenia or bipolar disorder, participation in any other trial, being pregnant or lactating, or no signed informed consent.

### Outcomes

The primary outcome of the study is HbA_1c_. Secondary outcomes are insulin resistance and beta-cell function measured by the homeostasis model of assessments (HOMA) and quantitative insulin sensitivity check index (QUICKI). Further secondary outcomes include the alteration of serum 25 (OH) D over time, blood pressure, lipid profile, parathyroid hormone, calcium, thyroid function, AGE accumulation in the skin, safety profile of vitamin D supplementation, urine analysis for microalbuminuria, and quality of life assessed by The Short Form (SF-36) Health Survey questionnaire.

### Sample size estimation

It was calculated that 126 patients with T2DM would be required in this trial to demonstrate a significant difference at 80% power and 5% significance. Power calculations were based on the literature and aimed at a difference of 0.5% in HbA_1c_ value in the treated group as compared to the placebo group with a standard deviation of 1.0% [30]. With an expected rate of 50% vitamin D deficient participants, 252 subjects would be required. According to an expected drop out rate of 20%, 300 subjects will be recruited.

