### Statistical analysis

The primary efficacy analysis to explore the intervention effect on glycaemic control will be based on the intention-to-treat (ITT) method, in which all randomised patients for whom outcome data are available, will be recorded. In the ITT analysis the patients will be analysed according to their original group assignment, whether or not they accepted and/or adhered to the intervention. This analysis avoids the possibility of any bias associated with loss, misallocation or non-adherence of participants. If there will be a substantial difference between those allocated to receive an intervention and those who actually received it (and adequately adhere to it), we will perform an additional analysis adjusting for actual treatment received (‘per protocol’ analysis). The results of the ‘per protocol’ analysis will be compared with the ITT analysis and the numbers involved will be precisely described.

All raw data will be entered into SPSS software (version 20.0, SPSS Inc, Chicago, IL). Ten percent of all data will be double-entered to check for duplication and outliers before starting statistical analyses.

Baseline characteristics of the study patients will be summarised separately for each randomised group. Dichotomous and categorical data will be presented as number and percentages of patients within both groups. Continuous variables will be checked for normality and will be presented in terms of means and standard deviation if normally distributed, or when a variable has a skewed distribution as median, 25th and 75th percentiles. Nominal variables including subgroups will be analysed using the Chi-squared test, ordinal variables by the Mann-Witney test or Kruskall-Wallis test and continuous variables by the *t*-test or analysis of variance model (ANOVA).

The primary efficacy endpoint, HbA_1c,_ will be compared between placebo and treatment group using a repeated measures analysis of variance with adjustment for baseline characteristics. For secondary outcomes a paired *t*-test, Wilcoxon’s test or repeated measures analysis of variance will be performed. Delta values will be calculated to compare the differences in means over time between the treatment and placebo group.

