This trial has several strengths: the study sample size allows us to perform a subgroup analysis of vitamin D deficient patients. Taken into account that only in vitamin D deficient patients an effect of vitamin D supplementation on glycaemic control will be found, we chose to recruit double the number of participants as calculated with the power estimation, hypothesizing that 50% of the included patients will be vitamin D deficient (serum 25 (OH) D < 50 nmol/l). Secondary, the relatively high dose chosen for intervention and the duration of the trial are strengths of our study. The dose of vitamin D supplementation of 50,000 IU of vitamin D per month (daily equivalent ~1667 IU) is based on the recommendations of the Institute of Medicine and on the study done by van Groningen et al. [31,34]. In this latter study, performed in the Netherlands, it was demonstrated that a cumulative dose of 100,000 IU given in 2 months increases the serum 25 (OH) D meanly with 29 nmol/l. Assuming that the mean serum 25 (OH) D in our study population will be around 50 nmol/l at baseline, the serum 25 (OH) D should be raising to a sufficient status (≥75 nmol/l) in two months. To measure a difference in HbA_1c_ level we hypothesize that the maximal effect will be seen at least at six months, regarding the fact that the red blood cells circulate about 100 days in the blood and HbA_1c_ levels takes around six weeks to change. Furthermore, this is the first study examining the association between vitamin D status and skin autofluorescence value as well as the effect on skin AGEs after vitamin D supplementation. For this secondary outcome the duration of our trial will be a limitation, regarding the stability and long half-life of skin AGEs with could be the cause to find no effect of vitamin D supplementation on skin AGEs.

The results of this trial should provide more insight into the potential causal association between vitamin D status and glycaemic control in patients with T2DM.

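### The stated 80% power belongs to the vitamin D-deficient half of the sample, while the primary analysis compares all randomised patients, for whom the plan's own inputs give about 49% before adjustment

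*Protocol article*

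**What the plan says.** Protocol article, Sample size estimation: "It was calculated that 126 patients with T2DM would be required in this trial". The stated target for this number is "to demonstrate a significant difference at 80% power and 5% significance". The calculation "aimed at a difference of 0.5% in HbA_1c_ value in the treated group as compared to the placebo group"; the SD it uses is given as 1.0%. The section continues: "With an expected rate of 50% vitamin D deficient participants, 252 subjects would be required". Its closing step allows for losses: "According to an expected drop out rate of 20%, 300 subjects will be recruited". It does not say to which population the 80% applies.

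The Discussion explains the doubling. It begins "Taken into account that only in vitamin D deficient patients an effect of vitamin D supplementation on glycaemic control will be found", and says that twice the calculated number is recruited because half of the participants are expected to be below 50 nmol/l. It presents the resulting size as a strength because it permits a subgroup analysis of deficient patients.

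Statistical analysis sets the primary comparison: "The primary efficacy analysis to explore the intervention effect on glycaemic control will be based on the intention-to-treat (ITT) method", covering every randomised patient with outcome data. HbA1c is compared by repeated measures analysis of variance, adjusted for baseline characteristics. The deficient group (15–49 nmol/l) appears only among the subgroup analyses. A second group, 15–35 nmol/l, is also called deficient there.

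**The concern.** Three statements do not fit together. The power figure is derived for 126 patients who respond. The sample is doubled because only half of those enrolled are expected to respond. The primary test then averages over responders and non-responders.

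A reader of the sample size section will take the 80% to be the power of the primary analysis. On the plan's own premise that analysis faces half the effect used in the calculation. Doubling the sample does not make up for this: halving the difference calls for four times as many patients, not twice as many.

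The interpretation of a null primary result is at stake. If 80% power is credited to it, such a result would look like fair evidence against an effect. Under the investigators' own hypothesis it could easily arise although vitamin D works in deficient patients.

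**Working it through.** **Inputs.** From Sample size estimation: difference 0.5%, SD 1.0%, 5% significance, 80% power, 50% deficient, 20% drop-out, 300 recruited. From Randomisation: 1:1 allocation. From the Discussion: no effect at or above 50 nmol/l. Sidedness is not stated. A two-sided test reproduces 126, while a one-sided test gives 100, so two-sided is used.

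**Step 1: reproduce the plan's figure.**
n per arm = 2 × (1.960 + 0.842)² × SD² / difference² = 2 × 7.849 × 1.0² / 0.5² = 62.8, so 63 per arm and 126 in total. This matches. Power at 63 per arm is 80.1% (79.5% by the t distribution). Then 126 / 0.50 = 252, which also matches. So 126 is the required number of deficient patients, and 252 is the number needed to obtain them.

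**Step 2: effect in the primary population.**
0.50 × 0.5% + 0.50 × 0% = 0.25%.

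**Step 3: unadjusted power for 0.25%, SD 1.0%.**
Power = Φ(difference / (SD × √(2/n)) − 1.960), with n per arm.

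| Evaluable | n per arm | Standard error | Difference / SE | Power |
|---|---|---|---|---|
| 240 (300 less 20%) | 120 | 0.1291 | 1.936 | 49.1% |
| 252 | 126 | 0.1260 | 1.984 | 51.0% |
| 300 (no loss) | 150 | 0.1155 | 2.165 | 58.1% |

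The t distribution gives 48.8%, 50.7% and 57.9%. For 80% power at 0.25%, n = 2 × 7.849 / 0.25² = 251.2, so 252 per arm and 504 evaluable in total.

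**Step 4: the deficient group.**
Half of 240 is 120, or 60 per arm. With 0.5% and SD 1.0%, 0.5 / √(2/60) = 2.739, and power is 78.2% (77.5% by t). It falls slightly short of 80% because 300 less 20% leaves 240, not 252.

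**Step 5: sensitivity with 240 evaluable.** The values varied in the first four rows are assumptions; the protocol does not give them.

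| Change from step 3 | Power |
|---|---|
| Baseline correlation 0.5 (SD × √(1 − 0.5²) = 0.866) | 60.9% |
| Baseline correlation 0.7 (SD × √(1 − 0.7²) = 0.714) | 77.4% |
| SD 0.7%, no adjustment | 79% |
| Effect of 0.1% or 0.2% in non-deficient patients | 64% or 77% |
| 47.8% deficient (Dutch figure for older people in the Background) | 45.7% |

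The correlation rows treat 1.0% as the SD of a single HbA1c value. The protocol does not say whether it is that or the SD of the change. If it is already the SD of the change, adjustment would add less.

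**The case against.** The strongest reply is that 49% is not the power of the test that will be run. It belongs to an unadjusted comparison of two means, whereas the plan adjusts for baseline characteristics and measures HbA1c at 0, 3 and 6 months. The SD of 1.0% comes from the literature. Entry requires a stable HbA1c of at most 8.0%, and 8.5% is a termination threshold, so the SD in this sample may be smaller. In combination these matter: an SD of 0.7% with a baseline correlation of 0.5 would give about 89%. This part of the objection stands. A reader might infer from 49% that the primary analysis is as likely as not to fail if the hypothesis is true. The document does not support that, because it fixes neither the correlation nor the SD in its own population. The 49% is what its sample size inputs imply.

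A second reply is that the absence of effect in non-deficient patients rests on one sentence in the Discussion, while the sample size section states 0.5% for treated against placebo without restriction. If 0.5% applied to everyone, power with 240 would be about 97%. That sentence is explicit, however, and without it the doubling would have no purpose.

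A third reply is that the intent is disclosed. An all-randomised primary analysis with a prespecified subgroup for which the trial was sized is a legitimate design, and its type I error is unaffected. That is right. A reader might go further and conclude that the primary population must be changed, or that the deficient-group result could carry no weight. Neither follows. Any testing order may be set in an analysis plan that is not shown. Promoting the deficient group also has costs: randomisation is unstratified, two cut-offs share the label deficient, the group's own power is about 78%, and recruitment is under way.

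The disclosure does not repair the power statement, which stands without a population beside a primary analysis to which it does not apply.

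**Conclusion.** The concern holds as a misattributed power figure. The 80% applies to 126 patients below 50 nmol/l, not to the all-randomised primary comparison. With 50% deficient, 0.5% in them, none in the rest and SD 1.0%, that comparison has about 49% unadjusted power at 240 evaluable, and at most 58% if nobody is lost. Baseline adjustment or a smaller SD would raise this by an amount the protocol does not let a reader determine. The assumed values tried one at a time give 61% to 79%, and in combination they can exceed 80%. The finding is therefore that the stated power is attached to the wrong population. It is not that the planned test is shown to have 49% power, nor that the choice of primary population is invalid.

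**What to change.** In Sample size estimation, state that the 80% refers to participants below 50 nmol/l at baseline, and that it is about 78% if 20% of the 300 are lost. Beside it, report the power of the all-randomised primary comparison as about 49% unadjusted under the same inputs. Add the range under named assumptions on baseline correlation and SD, and say whether the 1.0% refers to a single value or to the change. State in the protocol and the eventual report that a null all-randomised result will be read with that power in mind.

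This needs no extra patients and no change of analysis. Its only cost is a less favourable stated figure.

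The sponsor may also consider testing the group below 50 nmol/l first and all randomised patients second, in fixed sequence at 5% each. That would require one definition of deficient (15–49 or 15–35 nmol/l) and a decision before unblinding. The trade-off is that a miss on the first test, which has about 78% power, would block the all-patient claim.

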### Randomisation

A double-blind randomised placebo-controlled trial design has been chosen. Randomisation for the parallel treatment phase will be carried out by the pharmaceutical department after checking the inclusion- and exclusion criteria. The patient will be assigned to the treatment order as defined by the code. The patients will be randomised 1:1 according to the method of block randomisation with a block size of 10. No stratification is used. The study medication will be delivered in similar flagons and labels with its own sequence number. The allocation sequence number will be kept by the pharmacist in a secure place during the course of the study.

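### Recruiting 300 does not allow for 20% drop-out from a required 252: 315 would be needed, and 300 covers 16% loss, which costs about 2 points of power in the vitamin D deficient subgroup

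*Protocol article*

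**What the plan says.** The Sample size estimation section sets out a three-step chain.

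- **Base size.** "It was calculated that 126 patients with T2DM would be required in this trial" "to demonstrate a significant difference at 80% power and 5% significance". The calculation "aimed at a difference of 0.5% in HbA_1c_ value in the treated group as compared to the placebo group" "with a standard deviation of 1.0" per cent.
- **Doubling.** "With an expected rate of 50% vitamin D deficient participants, 252 subjects would be required".
- **Drop-out.** "According to an expected drop out rate of 20%, 300 subjects will be recruited".

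The Discussion gives the reason for the doubling. An effect is expected only in deficient patients (25(OH)D below 50 nmol/l), so "we chose to recruit double the number of participants as calculated with the power estimation". That sentence concerns the step from 126 to 252 and does not mention drop-out.

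The Statistical analysis section bases the primary efficacy comparison on every randomised patient with outcome data. It treats deficient patients as a subgroup. Allocation is equal: "The patients will be randomised 1:1 according to the method of block randomisation with a block size of 10".

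**The concern.** An allowance for drop-out should leave the required number after the expected loss. Here, 20% of 300 is 60, which leaves 240, not 252. The figure of 300 is close to 252 × 1.2 = 302.4 rounded down. That would mean 20% was added to the required number instead of the required number being divided by the retained fraction. The article does not show its route, so this is only the likely explanation.

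What is at stake is the power claim for the deficient half. The second step sizes that half at exactly 126, with no reserve, so any shortfall in the third step takes it below the stated power. Readers will use this justification to judge how informative a null result in deficient patients would be.

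**Working it through.** **Inputs** (Sample size estimation and Randomisation sections): difference 0.5%, SD 1.0%, power 80%, significance 5%, allocation 1:1, deficient share 50%, drop-out 20%. The article does not say whether the test is one- or two-sided. Two-sided is assumed because it reproduces the published figure; a one-sided test would give 50 per arm.

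**Step 1: base size.** n per arm = 2 × (1.960 + 0.842)² × (1.0/0.5)² = 62.8, rounded up to 63, or 126 in total. This matches the article.

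**Step 2: deficient share.** 126/0.50 = 252. This also matches.

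**Step 3: drop-out.**

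- Needed: 252/(1 − 0.20) = 315. The article has 300, a gap of 315 − 300 = 15.
- Left after 20% loss from 300: 300 × 0.80 = 240, which is 12 below 252.
- Loss that 300 can absorb: 1 − 252/300 = 16%.

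**Step 4: deficient subgroup.** Expected deficient patients among 240: 240 × 0.50 = 120, or 60 per arm.

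Normal approximation: power = Φ(0.5/(1.0 × √(2/n)) − 1.960).

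- n = 63: 0.5/√(2/63) = 2.806; 2.806 − 1.960 = 0.846; power 80.1%.
- n = 60: 0.5/√(2/60) = 2.739; 2.739 − 1.960 = 0.779; power 78.2%.

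| Deficient patients | Per arm | Normal approximation | t-test |
|---|---|---|---|
| 126 (required) | 63 | 80.1% | 79.5% |
| 120 (from 300 with 20% loss) | 60 | 78.2% | 77.5% |

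The loss is about 2 points by either method. Setting the t-test figure of 77.5% against the nominal 80% would mix methods, because the t-test gives only 79.5% at the full 126.

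**Step 5: all-patient comparison.** With 240 patients (120 per arm) and the stated 0.5% difference: 0.5/√(2/120) = 3.873; 3.873 − 1.960 = 1.913; power 97.2% (97.1% by t-test).

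**The case against.** The best case for leaving the text alone is that the consequence is small and uncertain.

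- **The deficient share is itself a guess.** There is no stratification or quota. Among 240 patients with an expected share of 50%, the standard deviation of the deficient count is √(240 × 0.5 × 0.5) = 7.7, so a shortfall of 6 is less than one standard deviation. A share of 126/240 = 52.5% would restore the full 126. This stands as a reason to call the effect small. It does not make the arithmetic right, because the plan's own inputs still do not lead to 300.
- **240 may be a low count.** HbA1c is also measured at three months, and the primary analysis is a repeated-measures model. A patient who leaves after month 3 might still contribute, and the article does not say. This also stands, so 240 is conditional on drop-outs having no usable outcome.

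A reader might infer the stronger claim that the whole trial misses 80% power. The documents do not support that. The primary comparison uses all patients with data, and 240 of them give about 97% power for the difference the plan names.

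It could be replied that the Discussion expects a response only in deficient patients, so that the all-patient difference is diluted. If the other half had no response, the average difference would be 0.5 × 0.5% = 0.25%. With the SD still 1.0%, power would be Φ(0.25/√(2/120) − 1.960) = Φ(−0.02), about 49%, with 240 patients. With 252 it would be Φ(0.25/√(2/126) − 1.960) = Φ(0.02), about 51%. Dilution is therefore nearly the same at either size. It is a separate question that the drop-out step neither creates nor would cure.

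**Conclusion.** The drop-out step is wrong as written, and the severity is minor. The first two steps reproduce exactly. The third does not: 300 is 15 below the 315 that a 20% drop-out requires, and it covers 16%. Nothing elsewhere in the article corrects it.

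The consequence is confined to the deficient subgroup. The expected number there falls from 126 to about 120, and power falls from about 80% to about 78% (79.5% to 77.5% by t-test). This rests on four assumptions: a two-sided test, exactly half of the patients deficient at the 50 nmol/l threshold, equal arms within the subgroup, and no outcome data from drop-outs. The figures are for an unadjusted comparison of two means, as in the plan's own calculation. The article gives nothing from which to compute any gain from baseline adjustment.

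**What to change.** Keep 300 and correct the sentence in the Sample size estimation section in one of two ways:

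- State that 300 recruited with 20% drop-out leaves about 240 evaluable patients, about 120 of them with 25(OH)D below 50 nmol/l, giving about 78% power for a 0.5% difference in that subgroup.
- State that 300 allows for a drop-out rate of 16%, if the sponsor considers that rate realistic.

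The first is the safer choice because it keeps the plan's own drop-out expectation. Either costs one sentence and changes nothing in the design or conduct of the trial. The only price is a slightly less favourable power or drop-out figure. Recruitment was still open when the article was written, so raising the target to 315 would also have closed the gap, but a 2-point loss in one subgroup does not require it.
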